**Primary Objective**

**Specific Aim 1**: Assess the feasibility of an Open-Label Placebo (OLP) for treating CRF in cancer survivors (CSs).

Hypothesis 1: An OLP will be perceived by the majority of CSs screened as credible and acceptable and we will meet our enrollment, retention and adherence targets.

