**3.0 INVESTIGATIONAL PLAN AND PROCEDURES**

**3.1 Study Design and Population**

We propose to conduct a pilot randomized-controlled, crossover trial to evaluate the feasibility, acceptability and effect of the open-label administration of placebo pills on CRF and associated psychosocial factors (e.g., emotional health, social health, quality of life, etc.) for cancer survivors (CSs) who have completed all cancer treatments yet continue to experience CRF. Additionally, in an exploratory manner, we propose to collect DNA saliva specimens that we intend to analyze in the future to identify potential biomarkers for predicting placebo responses.

To do this, we will use a 7-week, single site, two-parallel arm, randomized controlled crossover pilot study to determine the feasibility, acceptability and effects of an OLP on CSs who completed cancer treatments at least 6 months prior to enrollment in the study and report a fatigue score of 4 or greater on a 0-10 scale.

We will enroll 80 eligible CS participants who will be randomized into two groups of 40 (Group1 and Group2). In this crossover study, participants in Group1, will receive an OLP (placebo pill) for 21-days and Group2 (Observational Controls) will not. After a 1-week washout period, Group2 will receive the OLP for 21-days and Group1 (Observational Controls) will not (see Figure 1a: Study Design Schema).

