**3.5 Randomization and Interventions (if applicable)**

A randomized assignment will be placed in an envelope that will be opened by the intervention administrator during the participants’ first clinical site visit (Day 1 of the study). Until that time, the intervention administrator will be blinded to the randomized assignment until it is revealed to the participant. However, because of the “open disclosure” of placebo use, study assignments cannot be blinded to the intervention administrator or to the participant once the envelope is opened. To control bias, the intervention administrator will have limited contact with the participants after Day 1 with the exception of a brief “re-orientation” on Day 28 at the beginning of Period 2 .

On Day 28, participants originally assigned to Group2 will receive the OLP and be prescribed two placebo pills twice a day to take over the course of 3 weeks (21 days). The participants who were randomly assigned to Group1 will serve as the NO OLP observational controls over the course of 3 weeks (21 days).

Figure 2: Crossover Study Arms

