The delivery of the persuasive rationale will be audio-recorded in all patients for use in establishing fidelity to treatment. Because of the importance of the interaction between the intervention administrator and the participant, all interactions will take place in the context of a warm, supportive and natural interaction. The importance of the no-treatment control group will also be discussed and questions will be answered. After the placebo orientation, the envelope with the randomized assignment will be opened and both the participant and the intervention administrator will learn which group the participant will join.

**Group1**: Participants assigned to Group1 will be given a pre-filled, twice-per-day weekly pill organizer. The intervention administrator will instruct Group1 to “take 2 pills in the morning with breakfast and two pills in the evening before bedtime.” The placebo pills will be blue and maroon gelatin capsules filled with non-absorbable Avicel® (Microcrystalline cellulose), a common inert excipient for pharmaceuticals. Prior to departing, the participant will ingest two of the placebo pills and be given a medication diary with instructions to record each time placebos are taken so that a pill count can be made.

**Group2**: Participants assigned to Group2 will be reassured that they will receive the OLP during Period 2 of the study. The intervention administrator will also reiterate the importance of the role of observational controls.

Parking tickets will be stamped and participants will be provided contact information for study team member and IRB should they have questions or concerns. They will be given a reminder card with their next appointments (Day 21, Day 29 and Day 49). They will also be told to expect a follow up telephone call from a study team member midway through Period 1 on or about Day 11. The estimated time for the first clinical site visit (Day 1) is 60 minutes.

**Mid-Point Check-In Call:** participant is called to check on condition. Calls lasts < 5 minutes.

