**End of Period 1 (Day 21 of Study / 2nd Clinical Site Visit**): Study participants will be instructed to return to the clinical site on Day 21 of the study. At that time, the research specialist will collect the medication diaries and address any questions or concerns. The research specialist will administer the 4 questionnaires that will be labeled with the appropriate study identifiers and stored in a secured unit for future analysis. Participants will be reminded of their next clinical site visits (Day 29 and Day 49) and parking tickets will be stamped. Once again, participants will be reminded of the value of their participation. The estimated time for the 2nd clinical site visit is 25 minutes.

**Beginning of Period 2 (Day 29 of the Study / 3rd Clinical Site Visit):** On Day 29, participants will return to the study site to begin Period 2 of the trial. The research specialist will review the 4 questionnaires with the participant, address any questions or concerns and ask the participant to complete each instrument. The research specialist will label each completed questionnaire with the appropriate study numeric identifiers and store the questionnaires in a secured unit for future analysis. The intervention administrator will meet with participants to explain procedures for Period 2.

**Group1** : participants will be informed that they are now the OC and the value of that role will be reiterated. They will be reminded of their next clinical site visit and told to expect a follow up call at some point (on or about Day 39). Parking tickets will be stamped and the participant will be provided a reminder of the next (and final) clinical site visit (Day 49 of the study).

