**Statistical Analysis**

**Specific Aim 1:** We will evaluate the feasibility of recruiting and enrolling CSs into an OLP intervention.

Feasibility: among eligible CSs who inquire about our study, we will calculate the proportion of those who, after completing the screening procedure,

- sign the consent form;
- decline to participate;
- participate but drop out.

During the screening process, prospective enrollees will be asked 3 questions that pertain to credibility belief, outcome expectancies, and acceptability of an OLP. The rationale for asking these questions is to assess the feasibility of an OLP study for CSs, and whether credibility beliefs, outcome expectancy predict acceptability (which may have implications for selecting patients for future clinical trials). We will use an analysis of variance (ANOVA) to determine if credibility belief and/or outcome expectancy predicts acceptability.

- **Credibility Belief**: “Based on what I have said today, how logical does taking placebo pills to make help someone feel better seem to you?” Responses will range from 0 (makes no sense at all) to 10 (makes perfect sense).
- **Outcome Expectancy**: “At this point, how helpful do you think this treatment will be in reducing your fatigue?” Responses are measured on a 0% to 100% scale.
- **Acceptability**: “Based on my description of the study, are you still interested in participating?” Responses will be “yes” or “no”, or “not sure”. Those who respond “not sure” will be given 48-hours to decide if they wish to participate and will receive a follow-up call.

Acceptability: This will be determined proportionally by:

- **Accrual Rate**: baseline = 80 eligible participants
- **Retention Rate**: baseline = >75%
- **Adherence Rate**: placebo adherence by actual pill count and medication diary entries compared to an anticipated baseline rate of 100%.

For the analysis of acceptability, we will use a chi-square test, or Fisher’s exact test when the assumptions for the chi-square are not tenable. We will also apply log linear models if necessary to adjust for covariates.

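### The 100% adherence benchmark is not attainable in practice as a target, the named tests cannot assess it, and no pill count independent of the diary is described

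*Protocol*

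**What the plan says.** Section 2.0 of the protocol states the primary hypothesis. Besides credibility and acceptability, it predicts that "we will meet our enrollment, retention and adherence targets". Section 3.7 (Specific Aim 1, Acceptability) lists three rates with their benchmarks: accrual of 80, retention above 75%, and "placebo adherence by actual pill count and medication diary entries compared to an anticipated baseline rate of 100" percent. No other adherence figure appears, and nothing says what share of capsules makes a participant adherent. The same section continues: "For the analysis of acceptability, we will use a chi-square test", with Fisher's exact test as the fallback. It does not name the groups to be compared.

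Section 3.5 describes how adherence data arise. Each participant on open-label placebo receives a pre-filled organizer and a diary, with "instructions to record each time placebos are taken so that a pill count can be made". At the end-of-period visits on Days 21 and 49, "the research specialist will collect the medication diaries and address any questions or concerns". No step has the organizer or unused capsules brought back.

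**The concern.** Adherence is one of the three targets that Hypothesis 1 relies on, and section 3.6.4 makes feasibility and acceptability the primary endpoint. A target of exactly 100% has no room for a single lapse. Taken literally, it would be missed almost however well participants accept the placebo. Otherwise, the team would have to decide what counts as good adherence after seeing the data. Either way, the pilot gives a weaker basis for planning the larger trial that it is meant to inform.

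There are two related problems. The tests assigned to acceptability do not answer whether a rate reached a fixed value. And the pill count and the diary are listed as two measurements, while the visit procedures describe only one source, filled in by the participant. Participants have been told in the orientation that people who take their pills faithfully do better.

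**Working it through.** **Inputs from the protocol.** Section 3.1: "We will enroll 80 eligible CS participants who will be randomized into two groups of 40"; all are due to take placebo in one of the two periods. Section 3.5: "two placebo pills twice a day to take over the course of 3 weeks (21 days"). This gives 2 x 21 = 42 dosing occasions and 4 x 21 = 84 capsules per participant, or 84 x 80 = 6,720 capsules in all. The protocol does not derive the 100%, so there is no calculation to reproduce.

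**Inputs assumed.** The protocol gives no expected adherence rate, so a range is shown.

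**1. Can 100% be met?** Let p be the probability that a dosing occasion is taken, with occasions independent.

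- P(one participant perfect) = p^42. At p = 0.99 this is 0.656.
- P(all 80 perfect) = (p^42)^80. At p = 0.99 this is 2.2e-15; at p = 0.999 it is 0.035.

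Missed doses may cluster within people, so here is the same check without independence within a person. Let q be the probability that a participant is fully adherent. Then P(all 80 perfect) = q^80 and, if 60 remain, q^60.

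| q | all 80 | all 60 |
|---|---|---|
| 0.80 | 1.8e-8 | 1.5e-6 |
| 0.90 | 0.0002 | 0.002 |
| 0.95 | 0.017 | 0.046 |
| 0.99 | 0.45 | 0.55 |

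The target is realistic only if q is about 99% or more.

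**2. Fit with the retention benchmark.** Above 75% of 80 means at least 61 retained, so up to 19 may leave. Anyone who leaves while on placebo cannot reach 100% of 84 capsules if counted. The protocol does not say whether such participants are counted.

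**3. Denominator.** If adherence is read at the Day 21 or Day 49 visit before that evening's dose, a faultless participant shows at most 82/84 = 97.6%. This disappears if the denominator is capsules due by the visit, but the protocol does not say which applies.

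**4. Can the named tests assess 100%?** For a one-sample chi-square with null proportion 1 and n = 80, the expected non-adherent count is 80 x (1 - 1) = 0.

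- 80 of 80 adherent: that cell is 0/0, so the statistic is undefined.
- 79 of 80 adherent: the cell is 1/0, so the statistic is infinite.

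Fisher's test needs a second sampled group. Against an invented row of 80/80 it gives p = 1.00 for one non-adherent participant, 0.12 for four, 0.059 for five and 0.028 for six. A non-significant result would therefore not show that the target was met.

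**5. Sources of the pill count.** Section 3.7 lists an actual count and diary entries. Section 3.5 says that the diary is kept so that a count can be made, and that diaries are collected. Nothing in the visit steps would yield a count that differs from the diary.

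**The case against.** The best case for the plan has four parts.

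- **The 100% may be a reference, not a bar.** Section 3.7 calls it an anticipated baseline rate and treats acceptability as a matter of proportions. It could simply be the denominator of a descriptive percentage, and section 3.6.4 states no pass rule. This is a fair reading. But Hypothesis 1 then refers to an adherence target that appears nowhere, so the text needs correcting on either reading.
- **Chi-square and Fisher have proper uses here.** Section 3.6.1 asks whether randomized assignment is associated with retention, which is an ordinary two-group table, and section 3.7 adds log-linear models for covariates. This stands. A reader might infer that these tests are wrong for acceptability altogether; the protocol does not support that. They fail only for comparison with the fixed benchmark.
- **Adherence data are collected.** A reader might infer that the pill count is never obtained. That goes too far: diaries are kept for this purpose and are collected at Days 21 and 49. What is absent is a count independent of the diary.
- **The probabilities rest on assumed rates.** This is true, and clustering would raise the share of perfect participants above 66% at the same mean. The per-participant table needs no independence within a person and still leaves little chance unless nearly everyone is perfect.

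**Conclusion.** The point holds at moderate severity. As a target, 100% without tolerance is badly set: one capsule in 6,720 breaks it, and under assumed per-dose adherence of 99% to 99.9% the chance of meeting it is about 2e-15 to 3.5%. As a reference ceiling, it leaves the primary hypothesis without an adherence target. The named tests cannot judge a rate against it, and the two listed adherence sources come down to one self-report.

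A reader might conclude that the primary hypothesis is bound to fail. The documents do not settle that. They state no pass/fail rule for the endpoint, and the chance depends on adherence rates that they do not give. Nor do they show the retention benchmark to be defective. Randomization, safety and the Aim 2 comparison of fatigue and quality of life are not affected.

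**What to change.** 1. In section 3.7, replace 100% with a criterion fixed before data are seen: a stated share of participants taking at least a stated percentage of the capsules due by the visit. A threshold of 80% of capsules is only an example; the protocol offers no basis for a particular value. State whether participants who drop out on placebo are counted, and make Hypothesis 1 refer to this criterion.
2. Report adherence and retention against their benchmarks as one-sample proportions with exact 95% confidence intervals. For illustration, 72 of 80 adherent gives 81.2% to 95.6%. Keep chi-square and Fisher for Group1 versus Group2.
3. Leave the retention benchmark above 75% as it is. Requiring the lower confidence limit to exceed 75% would need 68/80 = 85% retained (lower limit 75.3%), which is a stricter target that nothing here justifies.
4. Have participants bring the organizer and unused capsules to the existing end-of-placebo visit (Day 21 for Group1, Day 49 for Group2), and count them separately from the diary.

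The cost is a protocol wording change and a few minutes of counting per participant at a visit already planned.

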**Secondary Objectives:**

**Specific Aim 2:** Evaluate whether an OLP reduces CRF severity and improves quality of life (QoL) in CSs compared to Observational Controls (OCs).

Hypotheses 2: Over the course of 49 days, CSs receiving the OLP will report significant declines in CRF severity and significant improvement in QoL scores compared to OCs.

**Supplementary Aim**: We will collect and store saliva samples so, should significant OLP effects be obtained, we can evaluate whether a potential biomarker (COMT Val158Met variant) associates with placebo responsiveness.

Hypothesis: The presence of the COMT Val158Met variations (met/met and val/val alleles) will correlate with the placebo responsiveness.

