**Group2** : participants will be informed that they will now receive the OLP. The intervention administrator will re-present a brief version of the rationale for the OLP and remind participants of the 4 main points from the original orientation meeting. Participants will be encouraged to ask questions and discuss concerns. Participants assigned to Group2 will be given a pre-filled, twice-per-day weekly pill organizer. The intervention administrator will instruct Group2 to “take 2 pills in the morning with breakfast and two pills in the evening before bedtime.” The placebo pills will be blue and maroon gelatin capsules filled with non-absorbable Avicel (Microcrystalline cellulose), a common inert excipient for pharmaceuticals. Prior to departing, the participant will ingest two of the placebo pills and be given a diary with instructions to record each time placebos are taken so that a pill count can be made. They told to expect a follow up call at some point (on or about Day 39). Parking tickets will be stamped and the participant will be provided a reminder of the next (final) clinical site visit (Day 49).The estimated time for the Day 29 clinical site visit is 35 minutes.

**Mid-Point Check-In Call:** participant is called to check on condition. Calls lasts < 5 minutes.

**End of Period 2/End of Study (Day 49):** Study participants will return to the clinical site on Day 49 of the study. At that time, the research specialist will collect the medication diaries and address any questions or concerns. The research specialist will administer the remaining questionnaires and assure that all questionnaires are stored in a secured unit for future analysis. The intervention administrator will meet briefly with participants to thank them for their participation and to distribute cash incentives. Parking tickets will be stamped. The estimated time for this visit is 25 minutes.

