**3.7 Statistical Methods**

The statistical analysis will be conducted under the direction of [name]. This pilot study will provide us important information concerning the acceptability and feasibility of OLP for treating CRF. It will also provide information on study design, retention and outcomes assessment.

**Power Calculation**: Our sample size calculations were based on minimal assumptions. Hence for each outcome, our planned sample size calculations indicated that we would have power of 80% assuming a two-tailed two-sample t-test on the outcomes at day 21, Type 1 error rate of 0.05, we would need a sample size of 80 to detect an effect size of 0.64. Techniques such as ANCOVA or two–sample independent t-test comparing change scores would be powerful or require less sample size to detect the same effect size depending on the correlation between baseline and follow-up measures

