**Specific Aim 2:** We will test the hypothesis that an OLP intervention reduces symptoms severity of CRF and improves quality of life for CSs compared to an observational control. The primary analysis for this aim will consist of mixed models repeated measures analysis, such as repeated measures analysis of covariance. This will allow the investigators to properly test for the absence of a carryover effect as well as account for the fact that all patients will receive both treatments (i.e., this type of analysis allows each patient to serve as his/her own control).

**Supplementary Aim:** evaluates the presence or absence of the COMTVal18Met genotype as a correlate for improved fatigue conditions and quality of life. We will measure this using a logistic regression model to determine associations. In addition, we will calculate the odds ratio and corresponding 95% confidence intervals.

**Multiple Comparisons Tests (Post Hoc Test):** To account for multiple comparisons, we will apply a Bonferroni procedure and control the family-wise error rate at .05.

**Missing Data**: Data deemed missing at random (MAR) will be handled using multiple imputation techniques with the Bayesian based Markov-Chain Monte-Carlo (MCMC) method. In supplementary analysis, we will use independent t-tests and chi-square to compare completers versus dropouts.

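### The Aim 2 two-period model cannot show absence of carryover as the protocol claims, and the Day 21 comparison, which is free of carryover, is not given a place in the analysis

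*Protocol*

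**What the plan says.** **Design (Protocol 3.1).** Two sequences, two periods, 40 participants each. Group1 takes open-label placebo (OLP) for 21 days and Group2 is observed. "After a 1-week washout period, Group2 will receive the OLP for 21-days and Group1 (Observational Controls) will not". No support is given for the length of the washout.

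**Analysis (Protocol 3.7, Specific Aim 2).** The primary analysis is a mixed-model repeated-measures analysis, with repeated-measures analysis of covariance as the example, in which patients act as their own controls. Of this model the protocol says: "This will allow the investigators to properly test for the absence of a carryover effect". It does not say what follows from the result of that test, or whether the Day 1 score or each period's own starting score is the baseline.

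**Sample size (Protocol 3.7, Power Calculation).** N = 80 rests on a "two-tailed two-sample t-test on the outcomes at day 21", with an effect size of 0.64 and 80% power. This is a Period 1 comparison.

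**Hypothesis 2 (Protocol 2.0).** "Over the course of 49 days, CSs receiving the OLP will report significant declines in CRF severity", compared with observational controls.

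**Delivery (Protocol 3.5).** On Day 1: "After the placebo orientation, the envelope with the randomized assignment will be opened". Both groups therefore hear the full rationale before Period 1. Before Period 2 the intervention administrator will "re-present a brief version of the rationale for the OLP" to Group2 only.

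**Measurements.** Questionnaires are completed on Day 1, Day 21, before Period 2 (Day 28 in Section 3.6, Day 29 in the visit descriptions of Section 3.5) and Day 49.

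**The concern.** In a two-sequence, two-period crossover, the carryover contrast on end-of-period scores is a comparison between patients. It cannot be separated from a sequence effect or a treatment-by-period effect. Failing to reject it says little, especially with 40 per group.

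Carryover is a live possibility here. Table 1 of the protocol describes the intervention as building expectancy and conditioning, and nothing in the protocol shows that these fade within a week. If Group1 keeps some benefit into Period 2, its control observations are improved by earlier OLP.

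The periods also differ by design. The Period 1 contrast is the pills and the pill-taking, because both groups have had the orientation. In Period 2, Group2 gets pills plus a repeated rationale, while Group1 has just come off OLP. Hypothesis 2 blurs this further: by Day 49 both groups have received OLP, so no untreated comparison group remains.

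What is at stake is the effect estimate. Section 1.0 says the pilot is to supply effect sizes and lead to a larger trial, and Section 3.6.3 makes the COMT evaluation depend on a significant OLP effect.

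**Working it through.** **Inputs.** From the protocol: 40 per group, d = 0.64 (SD = 1), two-sided alpha 0.05, retention target above 75% (about 30 per group at the floor). Assumed, because the protocol gives neither: within-person correlation rho between visits of 0.3 to 0.7, and a residual effect in Group1 of half (0.32) or all (0.64) of the treatment effect.

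**1. The protocol's own figure.** A two-sample t-test with 40 per group and d = 0.64 has power 0.807 (noncentral t). N = 80 is reproduced.

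**2. What each contrast estimates.** Let tau be the treatment effect, L the residual in Group1 at Day 49, and delta any extra effect of the repeated rationale in Period 2. Leave out period effects common to both groups, which cancel.
- Sum of Day 21 and Day 49: Group1 has tau + L and Group2 has tau + delta. The difference is L - delta, so carryover and the design difference between periods are mixed.
- Half the between-group difference in (Day 21 minus Day 49): [(tau - L) + (tau + delta)]/2 = tau - L/2 + delta/2.

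**3. Power to detect carryover (delta = 0).** The sum test has standardised effect L/sqrt(2(1 + rho)). The pre-Period-2 difference adjusted for Day 1 has standardised effect L/sqrt(1 - rho^2), with L now the residual at that visit.

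| n per group | Test | Half persists | All persists |
|---|---|---|---|
| 40 | Period sums | 12-14% | 34-42% |
| 40 | Day 28/29, unadjusted | 29% | 81% |
| 40 | Day 28/29, adjusted for Day 1 | 32-51% | 84-98% |
| 30 | Period sums | 10-12% | 26-33% |

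With 40 per group, the smallest residual that the sum test detects with 80% power is 1.02 to 1.17 SD, more than the whole planned effect.

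**4. Bias of the pooled estimate (delta = 0).** Let L29 and L49 be the residuals at the pre-Period-2 visit and at Day 49.
- End-of-period scores, or change from Day 1: tau - L49/2. Half persisting gives 0.64 - 0.16 = 0.48; all persisting gives 0.64 - 0.32 = 0.32. A simulation at half persistence (rho 0.5) gave 0.478 for the pooled estimate and 0.636 for the Day 21 comparison.
- Change from each period's own baseline: tau - (L49 - L29)/2. A constant residual gives no bias. If half is present at Day 28/29 and none at Day 49, the result is 0.64 + 0.16 = 0.80, or 1.25 times the truth.
- Covariance adjustment for the period baseline with slope b: tau - (L49 - b x L29)/2. With b = 0.6 (assumed), a constant residual gives 0.90 (half) or 0.80 (all) of the true effect.

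**5. The price of using Day 21.** The pooled SE is sqrt((1 - rho)/n). The Day 21 SE adjusted for Day 1 is sqrt(2(1 - rho^2)/n). Their ratio is sqrt(2(1 + rho)): 1.61, 1.73 and 1.84 for rho = 0.3, 0.5 and 0.7. At rho = 0.5 the two are 0.112 and 0.194. The adjusted Day 21 comparison still has 84-98% power at 0.64 with 40 per group.

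**The case against.** **The pre-Period-2 questionnaire gives a direct check.** This stands in part. The group difference at Day 28/29 is a randomised comparison made before Group2 starts OLP, so it is not mixed with the Period 2 differences, and it would usually reveal near-complete carryover. It remains weak for partial carryover and cannot establish absence.

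**The pooled model is more precise.** This stands. At half carryover and rho 0.5, the pooled analysis of end-of-period scores has 99% power against 90% for adjusted Day 21. Mean squared errors are about equal: 0.16^2 + 0.112^2 = 0.038 against 0.194^2 = 0.038. Day 21 wins on power only near full carryover (90% against 81%). Making it primary is a trade-off. It also isolates the pills, whereas the protocol regards the rationale as a key part of the intervention.

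**Sizing on Day 21 is not a contradiction.** This also stands. The protocol says its assumptions were minimal, and sizing a crossover on the simpler comparison is conservative.

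**Two stronger readings to avoid.** A reader might infer that a carryover pretest will choose the analysis and so inflate the type I error. The protocol states no such rule. A reader might also infer that the pooled estimate must be biased toward zero. That depends on the baseline, which the protocol leaves open, and on a residual effect whose size is unknown.

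**Conclusion.** The point holds in a limited form. The statement that the model can properly test for absence of carryover is wrong as written: non-significance never shows absence, and with 40 per group a residual of half the planned effect would be missed about 86-88% of the time on period sums and 49-68% of the time on the adjusted pre-Period-2 difference. The possible distortion ranges from halving the estimate (0.32 instead of 0.64, full persistence, end-of-period scores) through none to an overestimate (0.80, half present at Day 28/29 and gone by Day 49, own-period baselines). These sizes rest on the assumed correlation and residual effect; the documents do not show that carryover will occur. The 49-day wording of Hypothesis 2 does not fit a design in which both groups have had OLP by then.

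This should be fixed, but it does not threaten the trial's main purpose: feasibility is the primary objective and Aim 2 is secondary. It matters because Aim 2 supplies the effect sizes and decides whether the COMT evaluation goes ahead.

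**What to change.** 1. Delete the claim that the model tests for absence of carryover.
2. Report the Group1-Group2 difference at the pre-Period-2 visit, adjusted for Day 1, with its 95% CI, as a description of residual effect. State that it will not be used to choose the analysis. Give that visit one day number throughout.
3. Report the Group1 versus Group2 comparison at Day 21, adjusted for Day 1. It is free of OLP carryover and uses the time point on which N was sized. Preferably make it primary for Aim 2 with the two-period model as supportive; otherwise prespecify it as an estimate reported alongside that model.
4. State which baseline enters the two-period model.
5. Reword Hypothesis 2 to the 21-day treatment period.

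**Cost.** Wording only: no added participants, visits or measures. If Day 21 becomes primary, its standard error is about 61-84% larger than the pooled model's, although power at 0.64 stays at 84-98% with 40 per group. The Day 21 result must be described as the effect of the pills in people who have all heard the rationale.

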**3.6 Measures**

To qualify for the study, CSs must have a self-assessed fatigue severity level of >4 on a 0-10 scale with 10 being “extremely severe fatigue”. In addition to demographics, 3-questions will be asked during the screening process that will help assess feasibility and acceptability. OLP treatment effect will be measured with 4 questionnaires administered to participants Day 1 (Baseline) Day 21, Day 28 and Day 49 (End of Study). We will also determine the presence of the COMTVal18Met genotype.

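### Section 3.7 fixes single-step Bonferroni for multiple comparisons; Holm's step-down version keeps the same family-wise guarantee and rejects at least as often, so it is a cheap, optional gain in efficiency

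*Protocol*

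**What the plan says.** In the protocol's Section 3.7, under a general heading on multiple comparisons labelled post hoc, the plan commits to one method: "To account for multiple comparisons, we will apply a Bonferroni procedure and control the family-wise error rate at .05". The sentence follows the Supplementary Aim. It names neither Aim 2, nor a list of outcomes, nor the number of comparisons.

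The rule most naturally applies to Aim 2. Section 3.6 says that "OLP treatment effect will be measured with 4 questionnaires administered to participants", and Hypothesis 2 in Section 2.0 expects that "CSs receiving the OLP will report significant declines in CRF severity and significant improvement in QoL scores compared to OCs".

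The power paragraph of Section 3.7 sizes the trial "assuming a two-tailed two-sample t-test on the outcomes at day 21", with a "Type 1 error rate of 0.05", and concludes that "we would need a sample size of 80 to detect an effect size of 0.64". The planned Aim 2 analysis is different: a repeated-measures mixed model using both crossover periods. Section 3.6.4 makes feasibility and acceptability the primary endpoint.

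**The concern.** Single-step Bonferroni asks every p-value to beat .05/m, where m is the number of comparisons. Holm applies that threshold only to the smallest p-value and then relaxes it in steps, without weakening the error guarantee the protocol asks for. If the aim is family-wise control at .05, Bonferroni can therefore miss effects that Holm would declare at no cost in error rate.

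This has some bearing here. Hypothesis 2 claims both less fatigue and better quality of life, so more than one comparison must succeed. The enrolment target is fixed at 80. Significant OLP effects also trigger the genotype analysis of the Supplementary Aim.

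**Working it through.** **Inputs from the protocol.** Effect size d = 0.64; 40 per group; two-sided alpha .05; retention target above 75%, so 60 of 80 is used as the lower case. **Assumed, because the protocol does not state them:** m = 4 (one comparison per questionnaire), correlation 0.5 between outcomes, the within-patient correlation r between periods, and the number of outcomes that respond.

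**1. The plan's own figure.** The noncentrality of the Day 21 t-test is d·√(n/2) = 0.64 × √20 = 2.86 on 78 degrees of freedom. Power at alpha .05 is 80.7%, and 80% needs 39.3 per group, so 40. The stated total of 80 is reproduced.

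**2. Same guarantee.** Holm compares the ordered p-values with .05/m, .05/(m−1), ..., .05 and stops at the first failure. For m = 4 the thresholds are .0125, .0167, .025 and .05. With m₀ true nulls, the first one to be rejected stands at position m−m₀+1 or earlier, so its threshold is at most .05/m₀. A family-wise error therefore needs some true null with p ≤ .05/m₀, and the chance of that is at most m₀ × .05/m₀ = .05, whatever the dependence. In simulation with all four null, both methods gave a family-wise error of 0.050, 0.044 and 0.040 at correlations 0, 0.5 and 0.7.

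**3. Never fewer rejections.** Each Holm threshold is at least .05/m, so any p-value that passes Bonferroni also passes Holm. No Bonferroni rejection was lost in 40,000 simulated trials per setting.

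**4. Gain for the Day 21 t-test** (40 per group, d = 0.64, average power per responding outcome). At alpha .0125 the exact single-outcome power is 62.1%.

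| Outcomes responding (of 4) | Bonferroni | Holm |
|---|---|---|
| 1 | 62.3% | 62.4% |
| 2 | 62.0% | 64.3% |
| 3 | 62% | 67% |
| 4 | 62.3% | 71.8% |

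The chance of at least one rejection with all four responding is 89.2% for both. Holm's first threshold is still .05/m.

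**5. Gain for a two-period crossover analysis** (no carryover, all four responding). The noncentrality becomes d·√(N/(2(1−r))). For N = 80 and r = 0.3 it is 0.64 × √(80/1.4) = 4.84, against 2.86 above, so power is already high.

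| N | r | d | Bonferroni | Holm | Gain (points) |
|---|---|---|---|---|---|
| 80 | 0.3 | 0.64 | 98.8% | 99.7% | 0.9 |
| 80 | 0.5 | 0.64 | 99.9% | 100% | 0.1 |
| 60 | 0.3 | 0.64 | 94.2% | 97.6% | 3.4 |
| 60 | 0.5 | 0.64 | 99.0% | 99.8% | 0.8 |
| 80 | 0.3 | 0.40 | 68.3% | 77.6% | 9.3 |
| 80 | 0.5 | 0.40 | 84.3% | 91.2% | 6.9 |
| 60 | 0.3 | 0.40 | 52.2% | 61.2% | 9.0 |
| 60 | 0.5 | 0.40 | 69.7% | 79.0% | 9.3 |
| 80 | 0.3 | 0.30 | 38.7% | 46.4% | 7.7 |
| 80 | 0.5 | 0.30 | 55.3% | 64.5% | 9.2 |
| 60 | 0.3 | 0.30 | 27.9% | 33.6% | 5.7 |
| 60 | 0.5 | 0.30 | 40.9% | 48.8% | 7.9 |

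(20,000 simulated trials per row.) At d = 0.64 there is little left to gain. At d = 0.3 to 0.4 the gain is about 8 or 9 points in six of eight settings, and 6 to 7 in the other two.

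**The case against.** The strongest case against raising this is that Bonferroni is valid, standard and prespecified, and delivers exactly the family-wise control promised. The protocol nowhere claims the most powerful procedure. That stands, and it is why this is a suggestion and not a correction.

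A reader might infer that the plan gives power away for nothing. The documents do not support that. Bonferroni supplies simple simultaneous intervals that match its tests, and Section 1.0 says the pilot is meant to inform effect sizes. Intervals therefore have real value here.

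A reader might also take the Day 21 figures as the trial's expected loss. They belong to the sample-size simplification. The planned Aim 2 analysis uses both periods, and at the protocol's effect size the gain there is small. Nor does the protocol say that all four questionnaires must be significant together, so the larger gains on that criterion answer a question the plan does not ask.

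Finally, the protocol does not tie the rule to the Aim 2 outcomes or give m. Tying it to them is a reading, though a natural one. Holm's dominance for testing holds for any family and any m; only the size of the gain depends on them.

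**Conclusion.** The point holds as an optional improvement in efficiency. Holm keeps the family-wise level at .05 and never rejects less than Bonferroni.

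The benefit ranges from almost nothing to about 10 points of average power per outcome. It is near the top of that range for the Day 21 t-test at d = 0.64, or for a crossover analysis with a smaller true effect, in each case with every outcome responding. It is about 0 to 3 points for the crossover analysis at d = 0.64. It is 2 to 5 points in the Day 21 setting when two or three of four outcomes respond, and nil for the chance of any efficacy finding. All of this assumes m = 4 and the correlations shown.

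It would be wrong to conclude that the multiplicity rule is in error or that the main conclusion is at risk. The primary endpoint is feasibility and acceptability, which this choice does not touch.

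**What to change.** In Section 3.7, replace the Bonferroni commitment with a sentence such as: *The Holm step-down procedure, at family-wise .05, will be applied to the family of OLP-versus-control comparisons, and Holm-adjusted p-values will be reported.* Make the change before any outcome data are analysed.

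The cost is one sentence, with no extra patients, visits or data. The downside is the lack of equally simple simultaneous intervals. If Bonferroni intervals are kept for display (98.75% each when m = 4, since 1 − .05/4 = .9875), state that they are conservative and may include zero for an outcome that Holm rejects. If matching tests and intervals matter more to the sponsor than the extra rejections, keeping Bonferroni is defensible.
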